### The person-centred psychosis care intervention

The intervention is based on theoretical components of person-centred care. The person with psychotic illness is seen as a capable person who has a unique understanding of her- or himself, with unique experiences, expectations, needs, preferences, and resources [9, 22]. The success of implementation of complex care interventions depends partly on the ability to tailor the intervention to the existing care setting [23]. Therefore, we decided to use an approach built on Action Research principles [24, 25] where the patients, professionals, and researchers co-create the intervention to fit the specific care setting. The intervention was developed in two overlapping phases: an educational and experimental learning phase, and an implementation phase.

#### Educational and experimental learning phase

The educational and experimental learning phase (see Fig. 1) started in December 2014 and took place over a 20 week period. Ten staff participants from each of the four hospital wards were co-creators of learning. The group (*N* = 40) included psychiatric nurses, psychiatric carers, psychiatrists, social workers, occupational therapists, and a medical secretary. There was a planned structure for the learning phase and this was modified according to the needs of the participants. The educational intervention was led by a behaviour scientist specialising in culture change in large organisations with complex dynamics.

**Fig. 1 Fig1:**
[figure not shown]
The educational and experimental learning phase process

The participants were divided into cross-disciplinary learning groups that used an experimental approach in performing person-centred tasks such as person-centred dialogue with patients and writing person-centred care plans. Experimental learning or action learning can be described as an iterative process in which a problem is formulated, a plan of how to work in order to solve the problem is formulated, the new intervention is tested, and the results are analysed, documented, and reflected upon. If the intervention solved the problem it might become standard practice, but if it did not, then the process starts over again. A description of the educational intervention follows.

The educational intervention started with an introduction to theoretical components of person-centred care. Research findings from previous person-centred care studies carried out at somatic wards at the same hospital [12, 26–28] were presented along with ways to operationalize person-centred care components: building a partnership with the patient, using dialogue, co-creating a care plan with the patient, and documenting this care plan.

The staff learning groups planned the tasks to be performed until the following education day. The first task was to have a person-centred dialouge with a patient, write a person-centred care plan, follow up the care plan, reflect upon the task and decribe in writing the work with the patient and the care plan; what worked, and what did not work. The second task was to invite two colleagues who did not participate in the educational events for a free working lunch and discuss person-centred care. The participants were supported by a coach during these tasks if needed. The coach was a psychiatric nurse and had experience of working with other person-centred care projects and therefore could give feedback regarding difficulties the participants might have when performing their person-centred tasks.

Education days two and three involved presentations of the person-centred tasks that the learning groups had performed as well as giving and receiving feedback regarding these tasks. The learning groups also discussed possible new tasks that might make the work in their wards more oriented to person-centred care. The groups were presented with a scenario in which they had successfully developed person-centred care for two years and discussed questions such as: How does the co-operation between the inpatient wards and the outpatient units work now? When you reflect over the process that led you to this point, what was crucial to get you here? Then, the groups used their discussion to formulate one activity of change that could be performed in the wards immediately, and one activity of change that could be performed within three months.

The fourth and fifth education days started with follow-up and feedback regarding the person-centred tasks the staff had performed. Then, the participants were involved in a dialouge exercise in order to formulate a crucial question regarding an activity of change that they wanted the help of the whole group to answer. An Open Space dialouge followed around the questions: How are we going to perform person-centred care with our patients? What is a person-centred care plan? How do we want the co-operation between the inpatient care and outpatient units to work? How should we relate to our patients’ will and view of the world? How can we perform person-centred care with patients who undergo involuntary treatment? How do we need to develop our existing structures and roles in order to be able to work in a person-centred way? Which challenges have we discovered when we work in a person-centred way? Which risks might there be with person-centred care? These discussions were summarized and discussed further. Thereafter, the participants worked with an implementation plan of person-centred care. The starting point for this plan was the goal; person-centred patient work. The implementation plan included several steps such as: Which important steps towards the goal have we already taken? What do we need to do within one week? What do we need to do within one month? At the end of the fifth education day, the participants had an implementation plan to work with that contained activities to be performed in the short and longer term.

The last occasion for the education intervention started with following up on the activities of change that the learning groups had performed. A discussion about what constitutes successful change followed. The learning groups then continued to work with their implementation plans. They discussed challenges, resources, and co-operation partners. They also discussed how to follow up on their short- and long-term person-centred goals. The educational intervention finished with a summary of what had been accomplished during the intervention and each learning group had a tailor-made implementation plan to follow during the implementation process.

#### Implementation phase

The implementation phase overlaps with the first phase since successful experiences are shared with colleagues on the own ward as well as the other three wards. Thus, all staff on all four wards work with and further develop the PCPC intervention together with the patients.

To further assist the development of person-centred care activities and their implementation process, a steering group and an implementation group monitor the progress, taking action when needed. Clinical supervision sessions are provided to support continued experimentation with and implementation of person-centred interventions. Various aspects of person-centred care can be discussed in connection with lectures, seminars, and small group supervision sessions.

The implementation phase lasts for approximately three years, which allows staff to develop care interventions that promote patient involvement in the care. However, since person-centred care concerns an iterative process of culture change, there is no real end to the implementation process.

### Data collection and procedures

Before any data was collected, the Regional Ethics Board in Gothenburg approved the study. Pre- and post-intervention data are collected using self-report instruments, hospital registers, and interviews.

The participants are informed about the purpose of the study. They are also informed that participation is voluntary and (for patients and next of kin) does not affect the care, that the data is anonymous, that data is kept in a safe which only the research group has access to, that it is possible to withdraw consent without explanation, that results are reported so that the identity of the participants is protected, and that results are to be reported at conferences and in scientific journals.

#### Patient data

Shortly before planned discharge, a nurse or a psychologist included in the research group asks persons with psychosis disorders to complete research questionnaires related to outcomes and possible confounding variables (specified below). Some open-ended questions are also asked.

Since the data collection is carried out during inpatient care, all the usual management and safety mechanisms are in place. Should complications occur, these are reported at the usual clinical rounds.

The primary outcome measure is self-reported empowerment. The Empowerment Scale [29, 30] is validated and used internationally in studies involving persons with severe mental ill-health. There are 28 questions; responses are given on a Likert type scale ranging from 1 (agree totally) to 4 (disagree totally), and a higher score indicates a higher level of empowerment.

The secondary outcome measure is consumer satisfaction measured with the UKU-ConSat Rating Scale [31]. This scale contains 11 items; responses are given on a Likert type scale ranging from − 3 (very bad/negative/little) to + 3 (very good/positive/much). A higher score indicates a higher degree of satisfaction with care. The scale also contains a question on overall life experience and a question concerning mental health with the answer format 0 (worst imaginable) to 100 (best imaginable).

Possible confounders including illness burden, functional ability, and overall health are quantified for each patient at discharge. Positive and negative symptom burden are rated with the Remission sub-scale of the Positive and Negative Symptoms Scale consisting of 8 items reflecting core symptoms of schizophrenia [32]. Functional ability is determined using the GAF Scale [33] and overall health with the EQ-5D Scale [34].

Both during the pre- and post- intervention periods, experiences of care during the inpatient stay are explored in individual semi-structured interviews with a purposeful sub-sample of patients. Questions include: Please describe your experiences of the care you received. What did you perceive as helpful/problematic/difficult? Did you feel listened to? Were you included in decisions about the care?

#### Staff experiences

Staff’s experiences of the educational intervention and the implementation process are explored in focus group interviews. The interviews include questions about factors that are perceived to be valuable for the development of the new care model as well as factors that are perceived to be barriers.

#### Next-of-kin experiences

The next-of-kin are invited to participate in focus group interviews. Questions include: Please describe your experiences of the care your relative received. What did you perceive as helpful/problematic/difficult? Please describe your involvement in the care if you were involved. Did you feel listened to? All interviews are recorded and transcribed verbatim.

#### Ward level data

Overall ward burden is routinely measured with a standardized questionnaire in the context of quality monitoring at the Psychosis Clinic. Other ward level data including duration of inpatient care and number of days with involuntary treatment are obtained from electronic records in use at the clinic.

#### Project timeline

Figure 2 shows a timeline for the project. During the pre-intervention data collection, questionnaire and interview data was collected from patients together with quantitative ward data.

**Fig. 2 Fig2:**
[figure not shown]
A project timeline including information about data collected at different points in time

After the education intervention and during the implementation process, staff interviews were performed.

During the post-intervention data collection, questionnaire and interview data is collected from patients, interviews are performed with next-of-kin, and quantitative ward data is collected.

### Data analyses

Random data entry checks will be performed by a person who is in the research group but who is not involved with data entry to promote data quality. Missing continuous data will be dealt with in line with published instructions from the researchers who developed the different instruments. The distributions of the continuous variables will be examined to determine whether parametric (independent samples ANCOVA) or non-parametric (Mann-Whitney U-test) analyses will be employed when analysing group differences. The Chi-square test will be used to analyse dichotomised data. Two-tailed tests will be used and *p*-values less than .05 will be considered statistically significant. The focus group interview data will be analysed using methods for thematic analysis [35].

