**Methods/design:**

The care intervention will be assessed using a non-randomised trial with a before and after approach. The intervention involves an educational and experimental learning phase for hospital staff, followed by an implementation phase. The intervention is multi-professional; psychiatrists, psychiatric nurses, psychiatric carers, social workers, occupational therapists, and a medical secretary will be engaged in a participatory approach where they practice how to create a partnership and explore recovery-related goals together with patients. Patient-related outcomes include empowerment and satisfaction with care. Ward-level outcomes include daily ward burden, length of inpatient stay, and number of days with involuntary care. In addition, qualitative methods will be applied to capture patient, next-of-kin, and staff perspectives.

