### Power calculation

The primary outcome will be patient empowerment. A power calculation based on an independent samples t-test showed that a total sample size of 84 participants (42 per group in a balanced design) yields 80% power to detect a .2 difference in mean empowerment score between groups when “pre-intervention” and “post-intervention” scores are compared with a two-tailed test at a significance level of .05.

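### The look of the outcome distribution decides whether the primary before-after comparison can be adjusted for confounders at all

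*Protocol article*

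**What the plan says.** The abstract describes the design: "The care intervention will be assessed using a non-randomised trial with a before and after approach". Under Patient sub-study, separate groups of fifty patients are recruited before the intervention and after it is in place on all four wards.

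Under Patient data, the article states: "The primary outcome measure is self-reported empowerment". This is a 28-item score completed shortly before discharge. The same section adds: "Possible confounders including illness burden, functional ability, and overall health are quantified for each patient at discharge".

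The Power calculation section sizes the trial for a .2 difference in mean score: "A power calculation based on an independent samples t-test showed that a total sample size of 84 participants (42 per group in a balanced design".

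The Data analyses section then gives the rule for comparing the groups. The distributions of continuous variables are inspected to settle "whether parametric (independent samples ANCOVA) or non-parametric (Mann-Whitney U-test) analyses will be employed when analysing group differences". It gives no criterion for the choice, makes no exception for the primary outcome, and names no covariates for the ANCOVA.

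**The concern.** The two branches answer different questions. ANCOVA gives a covariate-adjusted difference in means. Mann-Whitney gives an unadjusted rank comparison.

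With independent groups recruited in different periods, patient mix may differ between them. The Implementation phase section puts implementation at about three years, so there is time for that to happen. ANCOVA is the only method the article names that can use the confounders it collects.

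The risk of confounding by period has nothing to do with the shape of the outcome, yet under this rule shape decides whether the primary result is adjusted. On the Mann-Whitney branch, the result also cannot be read against the .2 mean difference that justified the sample size.

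This is a rule the article states, not a detail left to an analysis plan. A plan that only added a normality threshold would leave the unadjusted fallback in place.

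**Working it through.** **1. The plan's own figure.** No SD is given, so 42 per group cannot be reproduced directly, but it can be solved backwards.
- Normal approximation: SD = 0.2 × √(42/2) / (1.960 + 0.842) = 0.2 × 4.583 / 2.802 = 0.327.
- Noncentral t: SD = 0.323, so the standardised effect is 0.2 / 0.323 = 0.62.
- If .2 were itself a standardised difference, 393 per group would be needed, so .2 is in scale points.

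**2. Bias when adjustment is dropped.** Bias in SD units = imbalance × correlation. The correlation of 0.5 and both imbalances are assumed.
- 0.3 SD imbalance: 0.3 × 0.5 = 0.15 SD; 0.15 × 0.323 = 0.048 points; 0.048 / 0.2 = 24% of the target difference.
- 0.5 SD imbalance: 0.5 × 0.5 = 0.25 SD; 0.25 × 0.323 = 0.081 points; 0.081 / 0.2 = 40%.

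**3. Each test on its own.** Simulation with no true effect, 50 per group, 3000 runs per scenario, one confounder treated as pure case-mix. Cells give false-positive rates at correlations of 0.3 / 0.5.

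| Outcome | Imbalance | ANCOVA | Mann-Whitney |
|---|---|---|---|
| Normal | 0 | 4.8% / 4.5% | 4.3% / 4.3% |
| Normal | 0.3 SD | 5.0% / 4.9% | 7.6% / 11.0% |
| Normal | 0.5 SD | 5.4% / 4.8% | 10.9% / 22.7% |
| Log-normal | 0 | 5.2% / 4.5% | 5.1% / 4.5% |
| Log-normal | 0.3 SD | 4.7% / 3.7% | 7.0% / 11.5% |
| Log-normal | 0.5 SD | 4.9% / 5.2% | 10.8% / 22.8% |

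Mann-Whitney's excess comes from the imbalance and is much the same with or without skew. ANCOVA does not exceed its level materially in the skewed scenarios, so the fallback was not needed for validity there.

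**4. The switching rule.** The article states no criterion, so a Shapiro-Wilk test at 5% in each group is assumed. Correlation 0.5, no true effect, 2000 runs:

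| Errors | 0.3 SD imbalance | 0.5 SD imbalance |
|---|---|---|
| Normal | 5.7% | 7.2% |
| Mild skew (gamma shape 16) | 6.4% | 9.6% |
| Moderate skew (shape 4) | 8.6% | 15.8% |
| Strong skew (shape 2) | 12.0% | 20.9% |

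Skew matters because it sets how often the rule lands on Mann-Whitney. With normal errors the gate does so in about 9% of runs, and 0.91 × 5% + 0.09 × 11% ≈ 5.5%, in line with the first row. A further run gives about 6% to 11% at 0.3 SD and about 8% to 26% at 0.5 SD; I take these as the working range. The upper ends move by a few points with the skew assumed: shapes 1 to 4 gave 10–13% and 17–28% in another set.

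**5. If the covariate is not pure case-mix.** Suppose the period difference in the covariate is caused by the intervention and the true total effect is 0.62 SD.
- 0.3 SD difference: ANCOVA estimates 0.62 − 0.15 = 0.47 SD. Power is 75%, against 85% for Mann-Whitney.
- 0.5 SD difference: ANCOVA estimates 0.62 − 0.25 = 0.37 SD (0.38 in simulation). Power is 54% against 85%.

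**The case against.** The strongest reply is that the harm needs two things together: a verdict of non-normality and an imbalance between periods. Nothing in the article points to strong skew, and a score over 28 items tends towards symmetry. With a near-normal score the rule mostly selects ANCOVA and the inflation is small. The Discussion also already calls the before-after design an important limitation. This stands as a limit on size and severity. It does not defend the rule, which still hands the decision to adjust to an irrelevant feature of the data.

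A reader might infer that ANCOVA is the unbiased benchmark and adjustment simply removes confounding. The article does not support that. The confounders are measured at discharge, after exposure to the care being evaluated, so symptoms, function and health may be affected by it. ANCOVA's 5% in the simulations follows from coding the covariate as case-mix.

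The covariates are also an inference, since Data analyses names none. It is a strong one: ANCOVA needs covariates, and independent groups measured near discharge have no individual baseline score.

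Two further readings go beyond the text:
- A reader might take "The Chi-square test will be used to analyse dichotomised data" as a second unadjusted effect analysis. The article names no dichotomised patient outcome, and the sentence may concern patient characteristics.
- A reader might say the check looks at the wrong distribution, because ANCOVA concerns residuals. The condensed sentence does not say which distributions are examined.

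**Conclusion.** The concern holds, at should-fix. The rule as written can remove confounder adjustment from the primary result of a non-randomised comparison and replace the powered mean difference with a rank test.

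Under the assumptions in steps 3 and 4 of the working, its false-positive rate is about 6% to 11% at a 0.3 SD imbalance and about 8% to 26% at 0.5 SD. The low ends apply to a near-normal score and the high ends to strong skew. With no imbalance there is no inflation. Imbalance, correlation, skew and the gate are all assumed, so these figures show direction and range and do not predict this trial's error rate. The documents do not show that the primary result will be unadjusted, only that it could be.

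**What to change.** For the primary outcome, delete the distribution-based choice. Specify one linear model (ANCOVA) of mean empowerment score on period plus prespecified, named covariates, with an HC3 robust 95% CI, used whatever the distribution. Report Mann-Whitney only as an unadjusted sensitivity analysis.

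Report the unadjusted mean difference beside the adjusted one. State that the covariates are measured at discharge, after exposure, and may themselves be affected by the intervention.

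The cost is a few sentences and slightly more analysis work, with no new data. The downside is that the adjusted estimate may remove part of any effect that acts through discharge symptoms or function, which is why both estimates should be shown.

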## Discussion

The current study employs a simple before and after design. While this is recognized as an important limitation, randomised control trials are not always optimal for assessing complex interventions in everyday clinical practice [23]. Randomising individual patients on the same ward (PCPC vs. standard care) was not considered an alternative as there would be a risk for “contamination” of the standard care situation as the intervention will introduce a new way of thinking about care practices. A traditional cross-over design is not possible as the intervention includes a pedagogical intervention for staff that cannot be “unlearned”. Randomising two of our wards to intervention and the other two wards to standard care would not provide sufficient power for a cluster study, and would be difficult since patients and staff sometimes move between wards which would “contaminate” the standard care situation. For a true evaluation of the effects of a person-centred educational intervention for care staff, another type of study design is required. The appropriate design would be a trial randomised at group level, a cluster randomised trial [23] in which random allocation is done at the cluster level (i.e. at the level of the service providers).

The fact that there are relatively few research studies of person-centred care in inpatient psychiatric settings, and in mental health settings in general [36] might be explained by these kinds of design problems which might deter researchers from studying outcomes of person-centred care. The lack of studies might also in part be explained by implementation problems. Smith and Williams [36] conducted a review and identified an important barrier to operationalise person-centred care practices, “the reluctance of service providers to fully embrace the principles of person-centred care, particularly the challenge presented by ‘empowerment’” (p. 296). To better meet potential implementation problems, we will tailor the PCPC intervention to the existing care setting and use a participatory approach in which the patients, professionals, and researchers co-create the intervention to fit the specific care setting.

For a number of reasons including thought disorder, paranoia and reduced insight, persons with psychotic illness may be particularly sensitive when it comes to participation in research projects. The intervention will be carried out during inpatient care and thus all the usual management and safety mechanisms are in place. Should complications arise, these will be reported at the clinical rounds. Each patient has an own contact staff person, who will communicate problems if and when they arise. The ability of the staff to be flexible and understanding of the psychotic individual’s situation is paramount, as is also the case in routine clinical care of persons with severe mental illness. Members of the research team have long experience of Research and Development projects involving this patient group. Care will be taken to ensure that participants are able to understand the meaning of the study and its procedures.

If this person-centred care intervention proves beneficial, the project may provide new directions for the planning of mental health services for persons with severe mental illness. The qualitative data will help to identify specific intervention components that are experienced as helpful or as barriers, from the perspectives of the individual patient, their relatives, and psychiatric staff. This is important as the planned intervention is complex in nature.
